## Abstract

**Background:**

*Plasmodium falciparum* malaria remains a major public health concern in sub-Sahara Africa. Seasonal malaria chemoprevention (SMC) with amodiaquine + sulfadoxine-pyrimethamine is one of the most important preventive interventions. Despite its implementation, the burden of malaria is still very high in children under five years old in Burkina Faso, suggesting that the expected impact of this promising strategy might not be attained. Development of innovative strategies to improve the efficacy of these existing malaria control measures is essential. In such context, we postulate that screening and treatment of malaria in household members of children receiving SMC could greatly improve the impact of SMC intervention and reduce malaria transmission in endemic settings.

**Methods:**

This randomized superiority trial will be carried out in the Nanoro health district, Burkina Faso. The unit of randomisation will be the household and all eligible children from a household will be allocated to the same study group. Households with 3–59 months old children will be assigned to either (i) control group (SMC alone) or (ii) intervention (SMC+ screening of household members with standard Histidin Rich Protein Rapid Diagnostic Test (HRP2-RDT) and treatment if positive). The sample size will be 526 isolated households per arm, i.e., around 1052 children under SMC coverage and an expected 1315 household members. Included children will be followed-up for 24 months to fully cover two consecutive malaria transmission seasons and two SMC cycles. Children will be actively followed-up during the malaria transmission seasons while in the dry seasons the follow-up will be passive.

**Conclusion:**

The study will respond to a major public health concern by providing evidence of the efficacy of an innovative strategy to boost the impact of SMC intervention.

## Background

Malaria remains a major public health concern in sub-Sahara Africa. According to the World Health Organization (WHO) nearly half of the world’s population is exposed to malaria infection causing 409,000 deaths worldwide in 2019 [1]. In Burkina Faso like in most sub-Sahara Africa countries, malaria is endemic with peaks during rainy seasons. To reduce the burden of the disease in the country, Burkina Faso has subscribed to the Roll Back Malaria initiative and adopted several malaria control measures including the use of artemisinin-based combination therapies (ACTs) as first line treatment since 2005, intermittent preventive treatment in pregnancy (IPTp), wide-scale distribution of long-lasting insecticide treated nets, and seasonal malaria chemoprevention (SMC) for children younger than five years [2]. However, despite the implementation of these multiple interventions, Burkina Faso is ranked among the top 10 countries carrying the highest malaria burden. For instance, in 2019, over 10 million clinical episodes and 1060 deaths were reported in the country [1].

In this context, new strategies to complement or to improve the impact of ongoing interventions are urgently needed in order to reduce malaria transmission. The study we propose aims at improving the effect of Seasonal Malaria Chemoprevention (SMC) intervention to achieve best impact in malaria control and elimination. SMC is one of the most important and reliable malaria preventive measures recommended by WHO and is known to reduce malaria morbidity by 30–83% [3–5]. It involves the administration of a combination of antimalarials, amodiaquine with sulfadoxine-pyrimethamine (AQSP) to children aged 3–59 months on a monthly basis during the high transmission season [2]. In Burkina Faso, SMC is implemented nationally from July to October by the National Malaria Control Program (NMCP) with the support of its technical and financial partners such as Global Fund, WHO, Malaria Consortium, President’s Malaria Initiative (PMI), and United Nations International Children’s Emergency Fund (UNICEF). SMC was firstly implemented in 2014 in 6 of the 70 health districts of the country. In 2018, national wide coverage was almost reached (except in Ouagadougou i.e. SMC was implemented in 60 health districts over 70 in total) and the intervention was considered to be adequately delivered by community health workers [6]. Since the adoption of this strategy, data assessing the real-life impact of this intervention in the country are sparse. In 2018, Druetz et al. reported a protective effect of 62% against clinical malaria in Burkina Faso. This study highlights the potential adding value of this intervention for malaria control though this protective effect appears far below the highest threshold of 83% reduction of malaria incidence expected from SMC intervention [7, 8].

The burden of malaria in children under five years old suggests that the expected impact of this promising intervention is not achieved. Indeed, children under five years old represented the most affected population accounting for about 90% of malaria cases. Rapid Diagnostic Test (RDT) confirmed malaria cases in the country increased from 1,219,975 cases, to 1,487,954, and 1,509,931, in 2016, 2017, and 2018 respectively [1]. In view of the actual trend, it becomes obvious that despite the implementation of this strategy, the burden of the disease and associated mortality is still very high in children under five in Burkina Faso, suggesting that the expected impact from this intervention is not achieved. This raises questions about other unknown factors that can negatively affect the effectiveness of SMC intervention. At the same time, huge efforts aiming at preventing human-vector contact were deployed such as the large-scale distribution of insecticide treated bed nets (LLIN). The latter are distributed on the basis of two individuals per LLIN unit. However, more than two individuals per bedroom is commonly observed in rural settings in Burkina Faso and most bedrooms are not adequate for the fixation of several LLINs. In addition, the frequent mosquito bites before sleeping time and changing mosquito behaviour becoming more aggressive before and after sleeping time is of concern [9, 10]. The latter could explain a persisting malaria transmission within a relatively close proximity despite full LLIN coverage.

Asymptomatic carriers of *P. falciparum* infection do contribute to the malaria reservoir, especially in highly endemic regions such as Burkina Faso, but no strategies currently exist aimed at draining this reservoir. In such circumstances, family members (e.g. mother, father, siblings and other relatives) living in the same room or house with children receiving SMC could continually sustain the transmission cycle despite existing measures such as the use of LLIN. According to the Nanoro health demographic surveillance system, an average of 3 inhabitants per household was observed [11]. Published literature on sleeping behaviour reported that children mostly sleep with their mother or with mother + sibling [12]. Attempts to improve the impact of SMC intervention includes its extension to children under ten years old which showed promising results in Senegal [13]. However, parents and older siblings (over ten years of age) not covered by the SMC (implemented either in under 5 or extended to under 10) sharing the same habitat could be parasites reservoir continuously infecting the most vulnerable group under SMC coverage [9, 10]. This is particularly important in a context of low coverage and compliance to LLIN use. Indeed, according to the household survey results in 2018 from the World Malaria Report, 54.5% of the population in Burkina Faso had access to LLIN while only 44.1% had slept under LLIN the night before the survey [1]. This phenomenon of continuous infection of children from parents and elder siblings would obviously jeopardize the expected impact of the SMC intervention and the global effort to control the disease.

The presence of parasite reservoir within the community represents a challenge for malaria control and elimination with even sub-patent infection contributing to the maintenance of transmission [10]. However, the detection of the reservoir remains difficult given the low sensitivity of routine RDT for the detection of low and sub-patent parasitemia (parasitemia not detectable by mircroscopy or RDT but detectable by polymerase chain reaction).

Finally, drug pressure, especially in wide scale community-based intervention such as SMC, could lead to a selection of mutant strains with decreased sensitivity to the drugs used, which could compromise the long-term effectiveness of the intervention [14, 15]. Therefore, sustainability of any intervention relies on monitoring the selection of parasite mutations associated with drug resistance.

All these aspects support the idea of this study which stands on the assumption that the screening of household members of children receiving SMC could greatly greatly contribute to improve the impact of SMC intervention and reduce malaria transmission in endemic settings. The primary objective aims to improve the impact of SMC intervention in terms of reducing malaria morbidity and mortality in children under five years through a new strategy consisting in a screening and treatment of household members of SMC children. Secondary objectives include the assessment of the the tolerance and safety profile of the added treatment to SMC, the impact of the new strategy on the circulating parasite population as well as determinant such as adherence to treatment, acceptability, and cost-effectiveness of the strategy.

## Methods

### Study area

The study will be carried out in the Nanoro health district (NHD) catchment area which is situated in the central part of Burkina Faso. The NHD covers 5 departments: Nanoro, Soaw, Pella, Siglé and Kindi. The study will be implemented in the southern shore of the dam of Soum comprising the coverage area of 4 health facilities of the department of Soaw (Soaw, Zoetgomdé, Kologkom, and Poessé) and of one health facility (Kokolo) of the department of Nanoro. Figure 1 represents the area within the NHD that the study will cover (Fig. 1). The study area encompasses an area of 205,85 km^2^ with an approximate population of 19,915 inhabitants in 2018 according to the health and demographic surveillance system of the CRUN [11]. Like other Sahelian zones, the study area is characterized by high malaria risk during the rainy season [16], making the area an appropriate place for SMC implementation.

**Fig. 1 Fig1:**
[figure not shown]
The study area within the Health district of Nanoro, Burkina Faso. Mapping of the Health District of Nanoro indicating the area where the study will be implemented

### Study design

This will be a randomized superiority trial in which children will be followed for two years. The unit of randomization will be the household and all eligible children from a household will be allocated to the same study arm to avoid confusion. The household will be defined as follows: one or several individuals living together within a shared habitat (house) and sharing basic needs, especially kitchen, and which recognizes the authority of a single person regardless of his/her gender. Households with children aged 3–59 months with at least one under 35 months of age living within the Nanoro Health and Demographic Surveillance System (HDSS) catchment area will be assigned to either (i) control group (SMC alone) or (ii) intervention (SMC+ household members screening with standard HRP2-RDT and treatment if positive). Figure 2 represents the trial profile highlighting the difference between the two study arms and key stages for the study implementation (Fig. 2).

**Fig. 2 Fig2:**
[figure not shown]
The trial profile indicating the flowchart of the study participant from enrolment in 2021 to close-out visit in 2023. Flowchart of the study participant from enrolment to close-out visit

### Study participants

The study population will be children under SMC coverage i.e. aged 3–59 months and members of their household (individuals of all ages) living within the Nanoro HDSS catchment area [10]. The intervention for this study will be the screening of households members (of children under SMC coverage) for malaria parasitaemia and treatment of positive cases with the aim to prevent continuous re-infections of children under SMC coverage from these reservoirs. Children will be followed-up for 24 months to cover two full consecutive malaria transmission seasons and two SMC cycles. Children who age out of the SMC program, i.e., whose age exceeds 59 months during the follow-up, will subsequently be considered as household members. Before the implementation of the year 1 first SMC round, a list of potential eligible households will be drawn from the HDSS database. Home visits will be performed to confirm the presence of the children and to assess willingness of the parents/guardians to participate in the study as well as willingness of all the household members to be screened and treated. Households with absent children or children whose parents/guardians and roommates are not willing to participate, will be replaced by other eligible households from the list. Enrolment of study participants will be made in parallel with the SMC first round after confirmation of the administration of the first dose of the SMC treatment.

### Inclusion/exclusion criteria

Inclusion criteria are: (i) Single household (not sharing the same concession with other households) with at least one child under 35 months of age under SMC coverage, (ii) household members residing within the HDSS catchment area, (iii) willingness of household members to be screened and treated, (iv) ability to complete the study follow-up period, and (v) written consent obtained from parents/guardian (vi) written consent/assent obtained from each household member.

Exclusion criteria are: (i) household with children under SMC coverage who did not receive the SMC (Amodiaquine-Sulfadoxine-Pyrimethamine) or sharing the same concession with other households, (ii) household with children under SMC coverage where at least one of his/her household members refuse to be screened and treated (these children will still receive the SMC treatment as part of their routine malaria prevention policy), (iii) severely ill individual at the time of enrolment including severe malaria (only individuals but household will be included), (iv) known allergy to AQSP for children and DHAPPQ for household members (the whole household will be excluded), (v) planned travel or inability to complete the study follow-up, (vi) participation in malaria vaccine trials or other therapeutic trials, and (vii) unwillingness to participate to the study.

### Sample size calculation

The aim of this study is to demonstrate that SMC for children between aged 3–59 months associated with the screening household members (through standard HRP2 RDT) and treatment if proven positive is superior to SMC alone in reducing the incidence of clinical malaria after 1 year. In this superiority trial the sample size is calculated to attain sufficient power to determine independently the relevant difference in malaria incidence rate between the control and the intervention arms, using classic RDT. The sample size estimation is performed under the assumption that the average number of malaria episodes per child aged between 3 and 59 months per year since the implementation of SMC in Nanoro health district varied between 1.38 and 1.76 [17–19]. Sample size of 236 in each arm will give at least 80% power to detect a 20% decrease in incidence of malaria after 1 year in comparison to a baseline incidence rate in the control arm (SMC) between 1.5–2.0 malaria cases per year, assuming a one-sided test with significance level of 0.025 and large samples z-test of the Poisson event rate difference (PASS software). To account for 10% study drop-out rate for any reason, the sample size will increase to 263 in each arm. Therefore, the final estimated sample size for this study is 526 households, with at least one child aged between 3 and 35 months to allow a follow up of the children during the study period and while benefiting of SMC. One child from each household (primary participants) will be included in the primary analysis, assuming that each household will have an average of 2 children under SMC coverage, about 1052 children under SMC coverage are expected [11]. The expected number of household members is estimated at about 1315 (263 × 5) under the assumption that each household from the intervention arm will have an average of 5 members. Data will be analysed with R software using the appropriate tests depending on the variables. Adherence to treatment and acceptability of the strategy (focus group discussion) will be assessed qualitatively.

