### Data collection

The proposed study includes two major interventions: the already existing and funded SMC intervention by the National Malaria Control Program and the newly proposed intervention (Household members screening and treatment) expected to boost the impact of the SMC intervention. For SMC intervention, complete dose (3 days regimen) of Amodiaquine + sulfadoxine-pyrimethamine will be administered monthly over a period of four months. Each monthly administration will be performed according to children age as follow: [3–11] months, SP: 262,5 mg/AQ: 76,5 mg on day 0, SP: 0 mg/AQ: 76,5 mg on day 1, SP: 0 mg/AQ: 76,5 mg on day 2, [12–59] months, SP: 525 mg/AQ: 153 mg on day 0, SP: 0 mg/AQ: 153 mg on day 1, SP: 0 mg/AQ: 153 mg on day 2. Administration of the fisrt dose will be supervised by the community health workers while the second and third doses will be administered under supervision of the study field workers. Household members screening for malaria and treatment with the combination of dihydroartemisinin-piperaquine (DHA-PPQ), is a study-specific intervention which will be implemented in parallel with SMC over the four months SMC period. Household members with positive RDT test will be treated with single daily dose of DHAPPQ over three days in accordance with the national guideline for malaria cases management as follow: [5–8[Kg, DHA 20 mg/ PPQ 160 mg, one tablet/day, [8–11[Kg, DHA 20 mg/ PPQ 160 mg, 1 + 1/2 tablet /day, [11–17[Kg, DHA 40 mg/ PPQ 320 mg, one tablet/day, [17–25[Kg, DHA 40 mg/ PPQ 320 mg, 1 + 1/2 tablet /day and for [25–36[Kg, [36–60[Kg,, [60–80[Kg and ≥ 80 Kg, DHA 40 mg/ PPQ 320 mg, two, three, four and five tablets/day respectively. Enrolled children in both control and intervention arms will be followed for 24 months to fully cover two consecutive malaria transmission seasons, including two SMC cycles, and two dry seasons. However, the superiority will be measured over one season of intervention. The analysis will be repeated on year 2 to look at similar impact with potentially a difference in transmission. Then a pooled analysis of 2 years intervention will be conducted. Children will be actively followed-up with monthly visits during each of the two malaria transmission seasons (July–December). At each visit, physical examination will be performed and anthropometric parameters will be recorded, including weight, height, and Mid-Upper Arm Circumference (MUAC). Weight will be measured with SECA 874 scale (SECA company ltd., Germany). SHAKIR strips will be used for MUAC measurement. Blood smears will be collected by finger prick for hemoglobin (Hb) measurement, malaria Rapid Diagnostic Test (RDT), microscopy and additional drop of blood will also be spotted onto filter paper for later PCR analyses. In SMC+ screening and treatement of household members with standard RDT study arm, SD Bioline Malaria Ag P.f (HRP2/pLDH), (Standard Diagnostics, Inc., Korea) will be used. A HemoCue® 201+ will be used for photometric measurement of Hb in g/dL in the field. Thick and thin blood films will be stained with Giemsa 3% for 30 min and examined with light microscope Olympus CX23. Malaria slides will be double-read by two independent microscopists. In case of discrepencies a third reader will intervein and the arithmetic mean of the two nearest densities will be considered as final results. A smear will be declared negative if the examination of 100 thick-film fields does not reveal the presence of asexual parasites. The later PCR analyses will be the genotyping malaria-positive blood samples for amodiaquine resistance molecular markers in *pfcrt* and *pfmdr1*, sulfadoxine resistance marker in *pfdhps*, pyrimethamine resistance marker in *pfdhfr*, piperaquine resistance marker on Plasmepsin 2–3 and artemisinin resistance markers in the propeller domain of the Kelch 13 (K13) gene on malaria-positive samples. Samples will be genotyped using established protocols to detect molecular markers of antimalarial drug resistance. Briefly, DNA extracted from the dried blood spots will be used as the template for amplification by polymerase chain reaction (PCR). To detect nucleotide sequence polymorphisms, cleaned PCR products will be sent to a commercial service for Sanger sequencing. Single-nucleotide polymorphisms (SNPs) will be called by comparison with the reference sequences using validated bioinformatics workflows. Gene copy number amplifications will be detected using previously published protocols [20]. Children presenting any infection other than malaria will be diagnosed and treated appropriately according to national standard of care practices. After the malaria transmission season, the follow-up will be passive during the dry seasons (January–June). Parents / guardians of the enrolled children will be asked to contact the research team based at the peripheral health facilities of the study area in case their child is unwell. During these visits, children will be diagnosed and treated according to national standard of care practices. Nevertheless, all children will be actively seen on month 24 for a study end visit. Table 1 summarises the activites for the participant assessment and follow-up troughout the study (Table 1).

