Superiority of the SMC + roommates malaria screening and treatment intervention over the routine implementation of SMC alone is expected. Therefore, the study will greatly contribute to identifying measures to reduce the malaria burden in Burkina Faso. By reducing morbidity and mortality, this study will have significant economic impact by promoting economic development and welfare in Burkina Faso, as malaria constitute an important threat to the development in the country.

We anticipate that holding SMC campaigns during the COVID-19 pandemic, combined with the fact that some parts of the country are prone to insecurity, may be challenging. However, it is important to stress that the 2020 SMC campaign has been fully implemented in the study area without any disturbance related to COVID-19 and/or security issue. In addition, the study area, Nanoro is located at 85 km from Ouagadougou, the capital city in the Central West Region of Burkina Faso, where we have not experienced any particular security issues so far.

Close monitoring of *P. falciparum* resistance markers to antimalarial drugs [24–27] will be conducted because the sustainability of any intervention, especially wide scale community-based intervention such as SMC, relies on the optimal efficacy of the drugs, especially as SMC induces a substantial drug pressure. Hence a close monitoring of the selection of resistance markers in the parasite population is paramount to describe the impact of the strategy.

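### The power statement uses control rates of 1.5 to 2.0, but the plan's own local rates are 1.38 to 1.76; at 1.38 the stated size gives about 77% power, not 80%

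*Protocol article*

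**What the plan says.** All of this is in the Protocol article, Methods, Sample size calculation.

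- The estimation is said to be performed under an assumption about the yearly number of malaria episodes per child aged 3 to 59 months, which, "since the implementation of SMC in Nanoro health district varied between 1.38 and 1.76". Three references are cited for this.
- The next sentence makes the power claim: "Sample size of 236 in each arm will give at least 80% power to detect a 20% decrease in incidence of malaria after 1 year". It is tied to a "baseline incidence rate in the control arm (SMC) between 1.5–2.0 malaria cases per year".
- The test is a large-sample z-test of the difference between two Poisson rates, one-sided at 0.025, computed in PASS.
- A 10% drop-out allowance raises 236 to 263 per arm, or 526 households in total. One child per household enters the primary analysis.

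The section does not say why the planning range differs from the cited range.

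**The concern.** Both ranges describe the same quantity: episodes per child-year under SMC in the study district. The first is presented as the basis of the calculation and the second is used in it. Between the two, the lower bound rises from 1.38 to 1.5 and the upper bound from 1.76 to 2.0.

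For a fixed percentage reduction, a higher Poisson event rate means more events and so more power. Both shifts therefore make the design look better. The lower bound matters most, because the smallest rate in the range determines how many children are needed for at least 80% power.

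A reader who takes the power claim together with the local evidence will conclude that the trial has 80% power wherever the control rate falls within local experience. If that is untrue at the low end, a non-significant one-year result would be read with more confidence than the design supports.

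**Working it through.** **Inputs (all from Sample size calculation).** Rate ratio 0.80; one-sided alpha 0.025 (z = 1.960); power 80% (z = 0.8416); one year of follow-up per child; 236 evaluable per arm; 10% drop-out; cited rates 1.38 to 1.76; planning rates 1.5 to 2.0. One child per household is analysed, so no clustering term is needed.

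**Formulas.** Let λ be the control rate, so the intervention rate is 0.8λ.

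- Size per arm: n = (1.960 + 0.8416)² × (λ + 0.8λ) / (λ − 0.8λ)² = 7.849 × 1.8λ / (0.04λ²) = 353.2 / λ
- Power with n per arm: Φ( 0.2λ / √(1.8λ/n) − 1.960 )

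**Step 1: reproduce the plan's figure.** At λ = 1.5, n = 353.2 / 1.5 = 235.5, which rounds up to 236. With drop-out, 236 / 0.9 = 262.2, which rounds up to 263. Both stated sizes are reproduced exactly, so the size was set by the lower planning bound of 1.5.

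**Step 2: power with 236 evaluable per arm.**

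| Control rate per year | Where it comes from | n per arm for 80% | Power with 236 |
|---|---|---|---|
| 1.38 | lower end of cited range | 255.9 | 76.7% |
| 1.50 | lower planning bound | 235.5 | 80.1% |
| 1.57 | midpoint of cited range | 225.0 | 81.8% |
| 1.76 | upper end of cited range | 200.7 | 86.0% |
| 2.00 | upper planning bound | 176.6 | 89.9% |

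Worked at 1.38: 0.276 / √(2.484/236) − 1.960 = 2.690 − 1.960 = 0.730, and Φ(0.730) = 0.767.

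**Step 3: where the claim stops holding.** The lowest control rate giving 80% with 236 per arm is 353.2 / 236 = 1.497. The part of the cited range below it is (1.497 − 1.38) / (1.76 − 1.38) = 0.117 / 0.38, about 31%.

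**Step 4: sensitivity to the test.** At 1.38, a test on the log rate ratio gives 76.6%. Simulating the z-test (2 million replicates) gives 76.9%. The result does not depend on the approximation.

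**Step 5: size of the gap in children.** For 80% at 1.38 the plan would need 256 evaluable per arm. Since 256 / 0.9 = 284.4, that is 285 enrolled per arm, against 263 planned.

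**The case against.** The strongest reply is that nothing has been miscalculated. The power sentence names its own range, and within 1.5 to 2.0 it is true; the document never says outright that power is 80% at 1.38. That stands: the fault is an unexplained planning range, not the arithmetic.

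The shortfall is also small and confined to one end. From about 1.497 upward, some 69% of the cited range, the claim holds, and the midpoint gives 81.8%. At 1.38, 80% power is still reached for a 20.8% reduction instead of 20%. If all 263 per arm were evaluable, power at 1.38 would be 81.1%. If drop-outs contributed half a year each on average (an assumption), about 250 child-years per arm would give 79.1%. These limits stand too. They do not remove the mismatch, because the plan attaches its claim to 236 after drop-out. The planned year 2 repeat and pooled analysis reduce the risk of misreading a null result, but the Data collection section says superiority is judged over one season.

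A reader might go further and infer that the trial lowers its own control rate below 1.38. In the Data collection section, "the second and third doses will be administered under supervision of the study field workers", apparently in both arms, and households whose children did not receive SMC are excluded. The Discussion, meanwhile, expects superiority "over the routine implementation of SMC alone is expected". The documents do not support that inference. They do not say how SMC was supervised, or how cases were detected, in the sources of the 1.38 to 1.76 figures. Monthly active visits with RDT and microscopy from July to December could raise recorded incidence. The net direction is unknown, so no control rate below the cited range is used here.

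**Conclusion.** The point holds as a mismatch between two ranges in adjacent sentences. With 236 evaluable children per arm, power runs from about 77% to 86% over the plan's own local rates and falls below 80% for control rates under about 1.5, roughly the lower third of that range. The largest shortfall is about 3 percentage points.

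This rests on the plan's own assumptions: Poisson counts, a full year of follow-up per evaluable child, a 20% reduction and a one-sided 0.025 test. A reader might also infer that extra-Poisson variation makes the true power much lower. It would lower power at every control rate, but the document gives no dispersion figure, and the question is separate from this mismatch.

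Nor does the finding show that the trial is too small or that 236 and 263 are wrong. They are right for 1.5. What needs correcting is the power claim when it is read against the evidence offered for it.

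**What to change.** Keep 263 per arm. In Sample size calculation, restate the power over the cited range, for example: *With 236 evaluable children per arm and Poisson counts, the trial has 77% to 86% power to detect a 20% reduction at control rates of 1.38 to 1.76 episodes per child-year, reaching 80% from a rate of 1.5.* Then either give the reason for planning on 1.5 to 2.0 or remove that range.

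The change takes one or two sentences. Enrolment, design and analysis stay as they are; the stated power becomes slightly less favourable at the low end.
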